### Outcome measures

Outcome measures are summarized in Table 2 and their psychometric properties in Additional file 3. Measures that were available only in English were translated into French with forward and back translation and a focus on conceptual equivalence [58, 59]. All purpose-designed forms are available in English and French. Measures of clinical, functional and subjective outcomes are administered at baseline and repeated for those who receive further treatment.

*Sample description*: Socio-demographic variables like sex, age, housing situation, ethnicity, and immigration background are obtained from a self-report form, clinical interviews, or records. Such data are crucial given the known social determinants of mental healthcare access and outcomes.

Where possible, items were picked to allow population-level comparisons, e.g., a Canadian census indicator of visible minority status [60] to help determine whether sites serve as many minority youth as the ethnic composition of their catchment populations would suggest they should.

A clinical profile of service recipients is created using a purpose-designed checklist of presenting concerns, the Global Assessment of Individual Needs-Short Screener [61], and the Columbia-Suicide Severity Rating Scale screener [62], among other tools..

*Service-level outcomes*: Forms were purpose-designed to record information about sites’ performance on key indicators pertaining to our three main hypotheses (increase in number of youth assessed, evaluation within 72 h, and adherence to the 30-day benchmark).

Data from these forms will also help identify barriers to meeting project benchmarks (e.g., delay due to lack of an on-site psychiatrist) and site-level quality improvement (e.g., information on referral sources will help tailor early case identification activities). Secondary questions can also be asked, e.g., about whether self-referrals increase over the course of the project. Staff will record on these forms up to three services needed by youth following the initial evaluation and services received by them 30 days later, which will serve as our measure of “appropriate” care.

Items taken from the Canadian Community Health Survey-Mental Health (CCHS-MH) 2012 survey [44] are used to determine whether youth are first-time help-seekers and the number and types of help-seeking contacts they make before entering a site (Hypothesis 4).

*Clinical outcomes*: To gauge the extent of clinical improvements, both self-rated and observer-rated measures are used. This includes the Kessler Psychological Distress Scale (K10) [63], a self-report measure of distress, and two self-rated single-item measures of physical and mental health [64, 65]. These measures are quick, easy to complete, validated, and used widely in clinical and population surveys, including in Canada [66]. The K10 is also used in Australian youth mental health hubs [67, 68].

Clinicians or trained research staff rate the severity of youth mental health presentations using the single-item Clinical Global Impression (CGI) scale [69]. Because youth present with highly diverse problems, anchor descriptions from the trans-diagnostic version [70] of the CGI were adopted. At all time points after the initial evaluation, staff also rate improvement in symptoms using the single-item CGI-Improvement. The CGI was chosen over more elaborate measures to increase clinician buy-in and rates of completion.

*Functional outcomes*: To examine if transformed services improve functioning, the Social and Occupational Functioning Scale (SOFAS) completed by clinicians or research assistants will be used. The SOFAS [71] is rated on a 1-to-100 continuum, without considering the severity of symptoms. In addition, the work/school status of youth is also being recorded.

*Subjective outcomes and well-being*: Three measures assess youth’s subjective progress and well-being following intervention — outcomes that were prioritized by youth members of the network.

The minimally burdensome Outcome Rating Scale assesses four dimensions of life functioning that indicate the success of therapeutic interventions [72]: individual well-being (measuring personal or symptom distress); interpersonal well-being (measuring functioning in intimate relationships); social role (measuring satisfaction with work/school and non-familial relationships); and overall well-being. At select sites, youth also complete the World Health Organization Quality of Life (WHOQOL-BREF) [73], a quick measure of perceived quality of life.

Given the larger goal of evaluating impacts for all youth across settings, most measures in our protocol are nomothetic. However, being a patient-oriented research project, it was thought important to include an idiographic measure inspired by the Goals Based Outcome (GBO) [74]. It allows youth to rate their progress toward three self-identified, personally salient goals during their follow-up. Family members/carers are also invited to choose and rate progress towards three goals in relation to their loved ones’ services. Pooled data on goal attainment will help evaluate the effectiveness of services, as has been done in the United Kingdom with the GBO [75–77].

*Service experiences*: To assess the extent to which ACCESS Open Minds transforms cultures of care, the youth and family versions of the Ontario Perceptions of Care (OPOC) [78] (a validated tool developed in Canada) will be used to assess satisfaction with the accessibility, quality and other aspects of services. Therapeutic alliance will be assessed using the Session Rating Scale (SRS) and youth’s perceptions of empowerment and engagement using the Youth Efficacy/Empowerment Scale [79]. These tools complementarily assess alliance with individual care providers (SRS) [80] and overall satisfaction with a service (OPOC).

### Data collection procedures

At all sites, data collection by trained clinical and research staff begins with referral and continues throughout follow-up, the length of which varies according to the needs of youth. Research assistants need 1 to 1.5 h to complete initial assessments and about 30 min for follow-up assessments. They have access to staff for help with any emergent crises.

In this study, “data” refers to data obtained directly from consenting individuals (e.g., self-reports) and non-identifiable data from pertinent health administrative records obtained with institutional approval. A secure electronic data capture and data management system makes the research/evaluation protocol accessible online from anywhere. Project staff, youth, and families can use the system to complete measures and forms on any device (desktop, tablet, or phone). Self-administered measures and forms can be emailed to youth/families for future completion on a user-friendly interface. The entire system — measures, forms, and interface — is bilingual (French and English). An integrated scheduling function facilitates follow-ups at time points as per the protocol. In case of connectivity issues, data can be collected offline and uploaded later. People who prefer completing measures/forms on paper can do so. Whether collected on paper or digitally, all data are entered into the electronic system.

Once data are entered, customized reports can be easily extracted to inform care in real time; e.g., clinical progress reports can support intervention decisions and goal attainment reports can help demonstrate improvement to youth. Dashboards within the software can be customized to display frequently sought information.

We expect to generate valuable insights into customizing and deploying electronic data capture and management systems in diverse real-world service and research settings. We will also seek to understand whether such a user-friendly system promotes measurement-based mental healthcare, which, despite its well-acknowledged value [41–43], is rare or inconsistent in Canada [81].

Periodic audits will be conducted at all sites to verify adherence to ethical and recruitment procedures, and to verify accuracy of data being collected. This audit will be undertaken by research team members based in a central coordinating office in Montréal. Central office staff also will regularly review electronic data to flag double data, data values not being in range, etc.

### Ethical considerations

Having obtained ethics approval from pertinent institutional bodies (see Additional file 4), the study is following appropriate regulations and standards regarding data privacy, confidentiality, storage, and security (see Declaration about “Ethics approval and consent to participate”). A checklist is being used to record adverse events (e.g., death by suicide, accidents, etc.), which are communicated to site and central institution ethics committees and to the project steering committee.

This study is being conducted according to Good Clinical Practice [82]. Appropriate procedures include informed consent from individuals, and institutional approval for access to pertinent non-identifiable health administrative records. Data are stored securely, and confidentiality of data will be ensured. A steering committee has been set up to oversee the project and provide inputs to the team of investigators.

ACCESS Open Minds acknowledges Canada’s problematic history of academic and administrative research on Indigenous peoples (outlined in the 1996 Report of the Royal Commission on Aboriginal Peoples) [83]. We follow the Ownership, Control, Access, and Possession (OCAP™) principles [84] and other precepts of the guidelines for Research Involving the First Nations, Inuit and Métis Peoples of Canada from the Tri-Council Policy Statement on Ethical Conduct for Research Involving Humans [85].

Within the ACCESS Open Minds project, OCAP principles are being implemented at all levels. Specifically, community leadership and the ACCESS Open Minds Indigenous Council have played integral roles in partnering with Indigenous communities, guiding conversations about the implementation of the research and evaluation protocol, and bringing together important voices and perspectives from the community. The OCAP principles are underscored in all research and partnership agreements held between the ACCESS Open Minds project leads and Indigenous communities. Most importantly, key decisions– from youth space design to how data will be analyzed and interpreted -- are being guided by Indigenous site teams, including the site team leader, Elders, youth, and other interested community members. OCAP also addresses the issues of privacy, intellectual property, data custody, and secondary use of data.

In ACCESS Open Minds, following Tri-council guidelines for research involving Indigenous peoples [85] is being seen not merely as a requirement, but as congruent with Indigenous self-determination and full-spectrum stakeholder engagement, both of which are critical in effecting lasting change in youth mental health outcomes in Indigenous communities. Finally, Indigenous communities participating in ACCESS Open Minds also respect the Jordan’s Principle [86] that guarantees equitable access to healthcare services for Indigenous children, regardless of the healthcare jurisdiction in which they live or access services.

### Sample size estimation

To arrive at the targeted sample size for catchment-area based sites (see Table 1), we used CCHS-MH-estimated percentages of the province's (a) youth who had a mental health/substance use disorder; (b) youth with mental disorders who sought help, and (c) youth with unmet needs for mental healthcare [87]. These were prorated to the site catchment’s youth population (i.e., number of youth aged 10 to 24 based on the 2016 Census [88]).

The estimate for unmet needs was added in furtherance of our primary objective of increasing case identification and thereby reducing untreated prevalence. Sites were to target reducing 20% of the unmet needs estimate per year in the project. Estimates for non-catchment area-based sites and for Indigenous community sites were arrived at in consultation with the sites.

The study protocol recommends that sites actively conduct outreach and other early identification activities; not turn away any youth; and approach all youth entering services for consent for research. At sites that have never participated in research, the percentage of youth who will provide consent cannot be estimated. It is therefore difficult to predict exactly how many youth will ultimately be included in our study. However, preliminary numbers from ongoing data collection suggest that 60% of youth approached will provide consent. It is estimated that the project will serve at least a total of 6029 youth. With a 60% consent rate, the estimated number of research participants from all 14 sites by the end of the project will be 3616. This should provide sufficient number or sample to answer the primary hypotheses.

### Statistical plan

Every attempt will be made to collect outcome data from all participants, including those who do not complete treatment. Youth will be considered as having a serious mental illness if they attain the relevant scale-specific cut-off scores on the K-10, SOFAS and/or the CGI-severity scale.

*Pre-post minimum evaluation protocol*: For each site, general linear models with repeated measures will be used to analyze differences over time per site (for hypotheses pertaining to increased referrals, evaluations within 72 h, treatment within 30 days, number of prior help-seeking contacts, and satisfaction with services) and per youth (at baseline and at follow-up timepoints for the hypothesis pertaining to improvements in functioning). Generalized estimation equations will be employed for parameter estimation. Respective baseline values will be added to the model as a covariate. Additional analyses will include examining hypothesis 3 separately for youth with and without serious mental illnesses, examining inter-site heterogeneity, and identifying baseline predictors of response to treatment. Finally, outcomes will be examined separately for large urban, small urban/rural and Indigenous contexts.

*Trial*: Youth demographics and clinical data will be described using means and standard deviations and trial waves will be compared using t-tests or non-parametric tests for quantitative characteristics. The effect of the interventions on the three primary and all secondary outcomes will be quantified using mixed or multi-level models to integrate cluster/wave and time effect. The unidirectional crossover design of the stepped-wedge trial allows us to test the effect of the intervention at both within- and between-cluster levels. Mixed models allow stratification (e.g., by population sizes); inclusion of missing data with the principle of intention to treat; and adjustment for baseline differences.

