### Secondary objectives

To determine if the ACCESS Open Minds model:
4.Simplifies pathways to mental healthcareHypothesis 4: Over the course of the project, youth will make fewer help-seeking contacts in the previous 12 months before accessing services at project sites.5.Improves outcomes for youth served at project sitesHypothesis 5: The clinical, social-vocational and subjective functioning of youth will significantly improve over the course of their follow-up. An additional objective is to determine which outcome domains are most impacted by treatment. The lengths of follow-up will vary depending on youth’s needs, severity of illness, etc.6.Satisfies youth and their familiesHypothesis 6: At least 75% of service users and their families/carers will be satisfied with services and service providers at all completion time-points.

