CCHS-MH 2012 questions related to services sought and received	Clinician-interview with youth and/or family/carer, plus any available records	Number of help-seeking contacts made for problems with mental health/substance use and whether or not services were received in previous 12 months (Hyp. 4)	None; can examine type of contacts (formal, informal, etc.)	Intake
*Clinical improvements*				
Kessler-10 Psychological Distress Scale (K-10)	Youth	Unidimensional factor of distress as being linked to mental ill-health and varied diagnoses (Hyp. 5)	Cut-offs based on overall score (e.g., mild distress)	Intake, Months 1, 3, 6, 9, and 12
Clinical Global Impression of Severity (CGI)^x^	Clinician	Clinician’s rating of severity of youth’s presenting problem over time (Hyp. 5)	None	Intake, Months 1, 3, 6, 9, 12 and 24/end of services
Self-rated health and self-rated mental health (SRH-MH)	Youth	Self-assessment of health and mental health, each on a single 5-item Likert scale (Hyp. 5)	None	Intake, Months 1, 3, 6, 9, and 12
*Functional improvements*				
Social and Occupational Functioning Assessment Scale (SOFAS)^x^	Clinician	Social and vocational functioning on a 0 to 100 scale (Hyp. 5)	None	Intake, Months 1, 3, 6, 9, 12 and 24/end of services
*Subjective/Well-being improvements*				
Goals tool inspired by the Goals-based Outcome (GBO) tool*^x^	Youth	Self-rated progress on 3 chosen goals (Hyp. 5)	None	Intake, Months 3, 6, 12 and 24/end of services
Outcome Rating Scale (ORS)^x^	Youth	Overall outcome/ functioning/ well-being (Hyp. 5)	None; Items related to overall; individual; interpersonal; and social outcomes can be examined separately	Intake, Months 6, 12 and 24/end of services
World Health Organisation Quality of Life – Brief (WHOQOL)*	Youth	Self-assessment of quality of life (Hyp.5)	Four domains: physical health, psychological health, social relationships, and environment	Intake, Months 6, 12 and 24/end of services
*Service experiences*				
OPOC^x^	Youth, family	Satisfaction (Hyp. 6)	Access to service, services provided, participation/ rights, therapists/support workers/staff, environment, discharge, recovery outcome, service quality	Months 1, 3, 6, 9, 12 and 24/end of services
Session Rating Scale (SRS)^x^	Youth	Working Alliance (Hyp. 6)	None; Items related to relationship; goals or topic; approach or method; and overall can be examined separately	Intake, Months 6, 12 and 24/end of services

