### Limitations

The potential of our stepped-wedge trial is limited because only six, very diverse sites were randomized to only three clusters. More, larger, and more similar clusters would have yielded a more robust trial [49–51]. Moreover, the dynamic, real-world nature of the transformation has posed practical challenges that impeded strict adherence to the timelines of our stepped-wedge protocol.

Two Indigenous sites, Ulukhaktok and Puvirnituq, were unable to follow the Minimum Evaluation protocol described in this paper because of cultural considerations, local constraints and preferences. They have also adopted a model that relies on local community workers to promote mental health literacy and wellness, and connect youth in need to supports, in lieu of hiring an “ACCESS Clinician”.

Across sites, the hesitancy of some inexperienced staff members to approach youth for consent could suppress sample sizes. The sheer diversity of local contexts and staff may result in reduced inter- and intra-site uniformity in recruitment and research assessment practices. This is being mitigated by creating a community of practice, conducting inter-rater reliability sessions, and providing training and support.

Our focus on evaluating the service transformation model in its entirety limits our ability to draw conclusions about the effectiveness of specific components. Our sample size and its distribution across 14 sites may preclude sophisticated analyses of the transformation’s differential impacts on different mental health problems. This will be mitigated by asking select questions about whether the model has different effects on presenting problems of differing gravity (mild-moderate versus serious).

Because the ACCESS Open Minds model involves the context-sensitive application of strategies to attain a set of five common objectives, the processes involved in service transformation and the extent to which objectives are attained can vary across sites. This is likely to influence the overall results. The actual processes of transformation at each site are being recorded and will be used to interpret results and to conduct additional explanatory analyses. Thus recording transformation processes will also provide rich, useful implementation data from diverse contexts that can inform similar initiatives in the future.

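### Hypothesis 5 credits the model with any improvement after intake, which regression to the mean or natural recovery could produce; severity contrasts on the same scales share the problem

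*Protocol article*

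**What the plan says.** All references are to the Protocol article.

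- **Secondary objectives.** Objective 5 is to determine whether the model improves outcomes. Its test, Hypothesis 5, is that clinical, social-vocational and subjective functioning "will significantly improve over the course of their follow-up". The hypothesis names no comparator.
- **Inclusion and exclusion criteria.** The study of outcomes is confined to youth who receive transformed services.
- **Statistical plan, minimum evaluation protocol.** Hypothesis 5 is analysed per youth, with baseline and the follow-up visits as time points. The baseline value is also entered as a covariate. Further analyses include "identifying baseline predictors of response to treatment".
- **Statistical plan, opening paragraph.** Youth are classed as having a "serious mental illness if they attain the relevant scale-specific cut-off scores on the K-10, SOFAS and/or the CGI-severity scale". The cut-offs, the visit at which they apply and the meaning of and/or are not given.
- **Table 2.** All three scales are Hypothesis 5 outcomes: K-10 ("Unidimensional factor of distress as being linked to mental ill-health and varied diagnoses (Hyp. 5"), CGI (the severity of the "presenting problem over time (Hyp. 5") and SOFAS ("Social and vocational functioning on a 0 to 100 scale (Hyp. 5").
- **Use of the split.** The Primary objectives and the Statistical plan both attach it to Hypothesis 3. The Limitations section adds a plan to ask "whether the model has different effects on presenting problems of differing gravity (mild-moderate versus serious", without naming an outcome. The Objectives section makes it a main question which youth groups benefit most and least.

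**The concern.** A person measured when unwell tends to score better next time, whatever the service does. Hypothesis 5 counts that movement as success, so an ineffective service could also meet it. The stated objective is about what the model does, and within-youth change among recipients of transformed care cannot answer that.

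The same mechanism threatens any comparison by severity. If a group is formed because its K-10, SOFAS or CGI score was extreme, and change on those scales is then compared, the extreme group drifts back further. The study could then report that the model helps seriously ill youth most when it helps nobody differentially. That would bear on one of the two main questions and on whom the model is scaled up for.

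**Working it through.** **1. The plan's own figure.** Expected participants: 6029 × 0.60 = 3617.4, against 3616 stated. The 14 site targets in Table 1 and its footnote sum to 3616 exactly. The figure reproduces. It bears only on precision; the plan states no SD, correlation, cut-off or effect size for Hypothesis 5.

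**2. Overall Hypothesis 5.** Let r be the intake-to-follow-up correlation. For each SD by which youth at intake stand above the level they regress to, the expected fall with no effect is (1 − r) SD. With r assumed at 0.5 to 0.7, that is 0.3 to 0.5 SD. The document does not say how far above that level youth present, so the overall drift cannot be sized further. Natural recovery would add to it.

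**3. Baseline as both response and covariate.** Write the response as Y(t) = a + b·t + c·G + d·t·G + e·B, with t = 0 at intake and 1 at follow-up, G the severity group and B the baseline score. Within a youth, Y(1) − Y(0) = b + d·G. B is constant over time and cancels, so d equals the raw difference in change. In every simulated setting below, the two agreed to three decimals.

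**4. Group cut on the outcome scale itself.** Scores are oriented so that high is worse (SOFAS reversed). With cut-off c in SD units and p = 1 − Φ(c), the groups differ at intake by φ(c)/[p(1 − p)] and at follow-up by r times that. The spurious difference in change is (1 − r)·φ(c)/[p(1 − p)].

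- c = 0.5: p = 0.309, φ = 0.352, ratio 1.65. Result 0.82 SD (r = 0.5) or 0.49 SD (r = 0.7).
- c = 1: p = 0.159, φ = 0.242, ratio 1.81. Result 0.91 SD (r = 0.5) or 0.54 SD (r = 0.7).

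**5. Three-scale rule, by simulation.** Assumptions: 400,000 youth, no mean change, no effect, cut-offs at 0.5 to 1 SD on any scale, r = 0.5 to 0.7, between-scale correlation 0.3 to 0.4. Two null models were used. In the true-score model each score is a stable level plus error. In the autoregressive model follow-up depends only on the same scale's intake score. Entries are in SD; grouping on the other two scales stands in for a separate measure.

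| Grouping | Null model | Change (or baseline as row and covariate) | Follow-up adjusted for own baseline |
|---|---|---|---|
| Outcome scale itself | either | 0.49–0.91 in favour of serious | about 0 |
| Any of three scales | true score | 0.19–0.33 in favour | 0.15–0.37 against |
| Any of three scales | autoregressive | 0.31–0.57 in favour | about 0 |
| Other two scales only | true score | about 0 | 0.18–0.42 against |
| Other two scales only | autoregressive | 0.16–0.37 in favour | about 0 |

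A between-scale correlation of 0.5 widens the three-scale change range to 0.18–0.61, hence about 0.2 to 0.6. With r = 0.9 the artefact shrinks to about 0.06 SD (three scales) or 0.16 to 0.17 SD (own scale).

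**6. Would it be declared significant?** Assume 300 youth per group and ignore site clustering. SE = √[2(1 − r)] × √(2/300).

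- r = 0.7: 0.775 × 0.0816 = 0.063. A 0.2 SD artefact gives z = 3.2.
- r = 0.5: 1.00 × 0.0816 = 0.082. A 0.6 SD artefact gives z = 7.3.

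**The case against.** **The split belongs to Hypothesis 3.** Both the Primary objectives and the Statistical plan say so. Whether care is offered within 30 days is not a change score on these scales, so the mechanism does not reach it. This stands. Use of the same groups for Hypothesis 5 is an inference from the Objectives, the Limitations and the predictor analysis. It is a natural inference, because the document has no other definition of serious, but no passage states it.

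**Baseline adjustment is planned.** This stands in part. If only follow-up scores were the response, the artefact would vanish or reverse. But the plan lists baseline among the per-youth time points as well as naming it a covariate, and in that form the covariate removes nothing.

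**The trial handles the comparator.** The Trial paragraph plans mixed models for all secondary outcomes, and the Study design says each cluster contributes data under both conditions. That is the right contrast, but Hypothesis 5 does not ask for it, and the inclusion criteria confine outcomes to transformed services. The Study design's remark that time trends can be countered statistically comes from its discussion of the stepped-wedge trial. It does not address drift within a youth after intake in the pre-post analysis.

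**An article condenses the plan.** Model details may sit in an analysis plan that is not shown. The wording of Hypothesis 5 and its link to the objective are fixed here.

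A reader might infer that regression to the mean alone will make the model appear to work best in serious illness. The documents do not support that. They do not commit to the contrast, the classification visit is unstated, and under follow-up adjusted for baseline the bias can be zero or run against the serious group.

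**Conclusion.** Hypothesis 5, as worded and as restricted to recipients of transformed services, can be met by regression to the mean or natural recovery. It therefore cannot by itself show that the model improves outcomes. This part needs no assumed figures.

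Any Hypothesis 5 contrast by severity or baseline predictor that uses the K-10, SOFAS and CGI groups inherits the problem. With baseline kept as a response, the spurious advantage to the serious group is about 0.2 to 0.6 SD for an any-of-three rule and about 0.5 to 0.9 SD for a cut on the outcome scale. This assumes no true effect, r between 0.5 and 0.7, between-scale correlations of 0.3 to 0.5 and cut-offs at 0.5 to 1 SD. None of these is in the document, and higher correlations over time shrink the artefact.

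Neither change nor baseline-adjusted follow-up is unbiased under both null models, so the answer, and even its sign, depends on an analytic form the text leaves open. The Hypothesis 3 split is not affected.

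**What to change.** 1. Report pre-post Hypothesis 5 results as observed change during care. Reserve the terms 'effect' and 'most beneficial' for contrasts between transformed and untransformed time, and state whether Hypothesis 5 data exist for untransformed time.
2. State whether the severity groups will be used for Hypothesis 5, at which visit they are set, and how and/or is resolved.
3. For any severity or predictor analysis of Hypothesis 5, do not keep baseline as both response and covariate. Report change and baseline-adjusted follow-up side by side, with a sensitivity grouping on a measure that is not the outcome, such as the GAIN-SS, which Table 2 already schedules at intake.
4. Claim a differential benefit only if these analyses agree. Under both null models in the table they do not, so the rule would correctly withhold the claim.

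The cost is wording and a little more analysis; no new data are needed. The Hypothesis 5 claim becomes more modest, and the sensitivity grouping will differ from the one used for Hypothesis 3.

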*Stepped-wedge trial*: Six sites were selected to participate in a randomized stepped-wedge trial [46, 47] wherein the intervention (a transformed service) was sequentially rolled out in three clusters/waves, starting six months apart. Sites were rank-ordered based on population, and the first three ranked sites were grouped as high and the last three ranked sites were grouped as low population. Thus stratifying by population size, two sites, one high-population and one low-population, were randomly assigned to each wave (see Fig. 1). At an event attended by representatives from all six sites, the randomization assignment was conducted by drawing chits from separate urns containing names of large and small sites (see Fig. 2).

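### Baseline tests between waves treat youth as independent although six sites were randomised, so their p-values would overstate imbalance (minor)

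*Protocol article*

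**What the plan says.** The trial part of the Statistical plan (protocol article) opens with description: "Youth demographics and clinical data will be described using means and standard deviations". The same sentence adds that "trial waves will be compared using t-tests or non-parametric tests for quantitative characteristics". No clustering term, site effect or multi-level version is mentioned for this comparison.

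The next sentence deals with effects. The three primary and all secondary outcomes are analysed with "mixed or multi-level models to integrate cluster/wave and time effect". The paragraph closes with a list of things that mixed models allow, among them "inclusion of missing data with the principle of intention to treat; and adjustment for baseline differences".

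On the units, Study design says "Six sites were selected to participate in a randomized stepped-wedge trial" and that "two sites, one high-population and one low-population, were randomly assigned to each wave". The Limitations section concedes that "only six, very diverse sites were randomized to only three clusters".

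**The concern.** What was randomised is the site, and each wave holds only two. Youth at one site share a catchment, a referral network and a service type, so their characteristics are correlated. A t-test or rank test on individual youth counts each as an independent draw, and stable differences between sites then appear as highly significant differences between waves. The plan allows for clustering in the outcome models but not in the sentence before them.

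At stake is what the baseline table tells its reader. Small p-values would suggest that the draw produced unusual imbalance, when two diverse sites per wave would give such values routinely.

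A wave comparison is also of limited use for the bias that matters most here. Study design says each cluster contributes observations under both conditions and warns of selection bias from unconcealed allocation. Randomisation took place in April 2015 (Fig. 2 caption) and the first participant enrolled in July 2016 (Participant recruitment), so every youth entered after allocation was known. Outreach is part of the intervention and may change who presents. The informative contrast is control-period versus intervention-period entrants within a site.

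**Working it through.** **The plan's own figure.** The article gives no alpha, ICC or power. The planning figure that can be checked is the expected number of research participants, 3616. From the consent rate: 0.60 × 6029 = 3617.4. From Table 1: eight listed targets, 277 + 864 + 93 + 236 + 700 + 329 + 39 + 865 = 3403, plus the minimum estimates in its footnote for the Indigenous sites, 68 + 56 + 44 + 23 + 17 + 5 = 213, total 3616. The figure is reproduced. The mean is 3616 / 14 = 258 per site.

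**Inputs.**
- From the article: six sites, three waves, two sites per wave, and the Table 1 targets as a guide to site size.
- Assumed: two-sided 5% level; ICC between 0.001 and 0.05; youth per site (m). The text available here does not show which six sites are in the trial (the wave configuration is in a figure), so m cannot be fixed.

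**Null hypothesis.** No systematic difference between waves beyond ordinary between-site variation. It is not the absence of site differences: that would mean ICC = 0, and the test would then reject at about 5%.

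**Formula, equal sites.** Design effect DE = 1 + (m − 1) × ICC. Actual rejection rate of the naive test = 2 × [1 − Φ(1.96 / √DE)].

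- m = 100, ICC 0.01: DE = 1 + 99 × 0.01 = 1.99; 1.96 / √1.99 = 1.389; rate 16.5%.
- m = 550, ICC 0.05: DE = 1 + 549 × 0.05 = 28.45; 1.96 / √28.45 = 0.367; rate 71.3%.
- m = 258, ICC 0.001: DE = 1 + 257 × 0.001 = 1.257; 1.96 / √1.257 = 1.748; rate 8.0%.

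| Youth per site | ICC 0.001 | ICC 0.01 | ICC 0.05 |
|---|---|---|---|
| 39 | 5.4% | 9.5% | 25% |
| 100 | 6.2% | 16.5% | 42% |
| 258 | 8.0% | 30% | 60% |
| 550 | 12% | 44% | 71% |
| 864 | 15% | 53% | 77% |

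**Unequal sites.** Each wave pairs a larger and a smaller site, so the equal-size formula was checked against the sum over waves of [ICC × Σn² / N² + (1 − ICC) / N], divided by the naive sum of 1 / N. The pairings are illustrative, using Table 1 sizes. For (864, 93) against (700, 236) at ICC 0.01:
- First wave: 0.01 × 755145 / 957² + 0.99 / 957 = 0.00928.
- Second wave: 0.01 × 545696 / 936² + 0.99 / 936 = 0.00729.
- Naive: 1 / 957 + 1 / 936 = 0.00211.
- DE = 0.01657 / 0.002113 = 7.84; rate 48%. At ICC 0.05, DE = 35.2 and the rate is 74%.

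For (277, 39) against (236, 44) the rates are 28% and 58%.

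**Simulation.** Three waves of two sites, 258 youth per site, ordinary t-tests on all three pairs. One pair rejected in 30% (ICC 0.01) and 61% (ICC 0.05) of tests; at least one of the three pairs rejected in 56% and 87% of trials. The single-pair rates agree with the formula.

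**The case against.** The strongest reply is that this sentence only describes the sample. The effect analysis is separate, uses mixed or multi-level models with cluster/wave and time, and does not depend on these p-values. That stands.

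A reader might infer more: that the tests decide which covariates enter the effect models, so that the primary estimates become data-dependent. The words "and adjustment for baseline differences" in the same paragraph invite this. The document does not support it. Adjustment is listed as something mixed models can do, and no rule links a test result to a covariate. A named covariate list is also detail that a condensed article may leave to the full protocol or analysis plan. What remains is narrower: the text does not rule such selection out.

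A reader might also take 16% to 71% as a prediction for this trial. It is not one. Alpha, ICC and the sizes of the six sites are all assumed, and Table 1 targets for the sites outside the Indigenous communities run from 39 to 865, so the possible span is wider at both ends.

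Nor is every rejection spurious. With six very diverse sites, many would reflect real differences between the particular sites in each wave. The fault is that the p-value is calibrated to sampling of youth, not to random allocation of sites.

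Two further criticisms carry little weight. That a t-test compares two groups while there are three waves is not decisive, because the wording permits pairwise tests or a multi-group rank test, though the usual forms of both ignore clustering too. And the plan does not say which youth enter the wave comparison, or offer it as a check on case mix at crossover, so it cannot be faulted for failing at that task.

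**Conclusion.** The point holds in limited form and is minor. Followed as written, the wave comparison is made at the wrong unit, and its p-values would exceed the nominal error rate for any positive ICC. The direction is certain; the size depends on assumptions. It is about 16% to 71% per test at a 5% level with ICC 0.01 to 0.05 and 100 to 550 youth per site, and about 8% at ICC 0.001 with 258 youth per site. The consequence is an overstated impression of imbalance in the baseline table. The documents give no ground for saying that the primary estimates are biased or data-dependent; they would be touched only if covariates were picked from these tests.

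**What to change.** Remove the significance tests between waves. A test that respected the six randomised sites would have almost no information with two sites per wave, so a corrected test is not a useful replacement. Instead:

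- tabulate youth characteristics by site and wave and, within each site, by control-period versus intervention-period entry, with standardised differences;
- add one sentence stating that adjustment covariates are not chosen from baseline p-values.

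The cost is the rewording of one sentence, that added statement and a different table layout. Sample size, data collection and the outcome models do not change.
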